### Sample size {14}

Maximal planned follow-up in the study will be 36 months (3 years). The 2-year rate of admission with first episode of infection or death in our patients on maintenance haemodialysis from 2000 to 2014 was 60%. In order to achieve a study power > 80% at 5% significance level in detecting a 30% reduction (from 60 to 48%) in the rate of first hospitalisation with all-cause infection or death, using the log-rank test (time-to-event modelling) assuming a 5% drop-out rate, 576 participants will be randomised 1:1 into each arm. The study also has > 90% power at 5% significance level of detecting a difference in haemoglobin of 5 g/L and standard deviation of 11.3 g/L based on published data [44, 45]. The sample size also provides enough power to determine differences within the ferritin strata.

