#### Analysing primary and secondary outcomes

Primary and secondary endpoints will be analysed according to the intention-to-treat principles (All participants data will be analysed according to the treatment allocation, regardless of what treatment they received and either they completed the follow-up or not).

The dichotomous primary outcome and all the dichotomous secondary events will be analysed using time-to-first-event regression using Cox proportional hazard models where the duration of the follow-up will be censored at the first between: date of outcome of interest, end of study, date of withdrawal (including withdrawal due to change in renal replacement therapy modality) or lost to follow-up. Given that these are competing events, sensitivity analysis will include analysis using Fine and Gray regression models [49]. The effect of the intervention will be estimated as compared to placebo using hazard ratios with corresponding 95% confidence intervals and *p* values. Recurrent event outcomes (i.e. rates of hospitalisation) will be analysed using the method of Ghosh and Lin [50] or, as an alternative, using random effects log-binomial models or one of the extensions of the Cox proportional hazards model [51, 52]. The approach choice will be guided by the distribution of the time to event and results of goodness of fit statistics.

Continuous outcomes assessed at multiple time points (e.g. haemoglobin) will be analysed using linear mixed models with a fixed effect for study allocation arm and time point and a random intercept to model the correlation of measurement taken within the same individual.

All the models will be univariable and include treatment arm only as independent variable (linear mixed models will also include a variable for time each outcome repeat was recorded).

Sensitivity analyses using a multivariable model to adjust for potential confounders will be performed when these factors appear to be not equally distributed between the two allocation arms.

*Pre-defined secondary stratified analyses* will be performed, comparing the effect of treatment between allocation arms according to:

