(i)The presence of active hepatitis B carriage (defined dichotomously by the presence of either measurable hepatitis B DNA according to PCR by the ABBOTT REALTIME HBV assay, or Hep B surface antigen positivity measured according to immunometric immunoassay (serum), at any time during the study).(ii)Average weekly haemodialysis attendance over the time included in the study, defined as an ordinal variable [in three groups: < 2.0 sessions/week, 2.0–2.75 sessions/week, > 2.75 sessions/week] for stratified analysis, as well as incorporated in Cox regression models with an interaction term between attendance group and treatment allocation group, as well as separately as an additional continuous variable in Cox proportional hazards regression modelling.(iii)Baseline ferritin threshold (≤ 1200 μg/L and > 1200 μg/L)(iv)According to presence/absence of comorbidities (diabetes, cardiovascular and cerebrovascular disease, lung disease).

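### For baseline ferritin, comorbidity and hepatitis B the protocol states only stratified arm comparisons, which do not test whether the treatment effect differs between strata; an interaction term is named for dialysis attendance alone

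*Protocol article*

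**What the plan says.** The protocol article, under Analysing primary and secondary outcomes, announces pre-defined secondary stratified analyses "comparing the effect of treatment between allocation arms according to" four factors: hepatitis B carriage, average weekly dialysis attendance, baseline ferritin split at 1200 μg/L, and comorbidities.

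The factors are not treated alike. Attendance is to be analysed by strata and is also to be "incorporated in Cox regression models with an interaction term between attendance group and treatment allocation group". The ferritin entry gives only the threshold. The comorbidity entry reads "According to presence/absence of comorbidities (diabetes, cardiovascular and cerebrovascular disease, lung disease" and stops. The hepatitis B entry defines the variable. None of these three mentions an interaction.

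The same section says that models will contain treatment arm as the only independent variable (plus time in the linear mixed models), with multivariable adjustment kept for sensitivity analyses. Effects are reported as hazard ratios with 95% confidence intervals and p values.

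The Sample size section adds: "The sample size also provides enough power to determine differences within the ferritin strata". It gives no figure and names no outcome for that claim.

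**The concern.** A Cox comparison of the arms within one stratum has the null hypothesis that treatment does nothing in that stratum. Whether treatment acts differently above and below 1200 μg/L is another hypothesis, and it needs an estimate of the difference between the two log hazard ratios. Two separate p values cannot supply it. Each stratum carries only part of the events, so one can reach significance and the other miss it through sampling variation alone.

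Ferritin is where this matters most. It is a randomisation stratifier, and high ferritin is the reason for the trial. The Abstract hopes that the results will lead to guidelines. A finding that iron helps on one side of 1200 μg/L and not on the other is one that a guideline group would notice. Yet the one factor given an interaction is attendance averaged over time in the study, which is a post-randomisation variable.

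**Working it through.** **Inputs (Sample size section)**
- Control risk: "The 2-year rate of admission with first episode of infection or death in our patients on maintenance haemodialysis from 2000 to 2014 was 60"% at 2 years.
- Target: "a study power > 80% at 5% significance level in detecting a 30% reduction (from 60 to 48"%), "using the log-rank test (time-to-event modelling"). A two-sided 5% level is assumed.
- Size: "assuming a 5% drop-out rate, 576 participants will be randomised 1:1 into each arm". This is read as 576 in total, as the Abstract states.
- Ferritin split: not given. I assume 50:50 and show other splits.

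**1. Reproduce the plan's figure**
- Hazard ratio = ln(0.52)/ln(0.40) = 0.714.
- Two-proportion formula, 60% vs 48%, 80% power: 270 per arm, 540 in total. 540/0.95 gives 569, close to 576.
- Evaluable patients: 576 × 0.95 = 547. Events at 2 years: 547 × (0.60 + 0.48)/2 ≈ 295.
- Schoenfeld power: Φ(0.337 × √295/2 − 1.96) ≈ 83%. The stated power above 80% is reproduced.

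**2. Range for the events.** With exponential hazards and follow-up spread evenly from 6 to 36 months (an assumption), the event probabilities are 0.527 (control) and 0.420 (iron). The total is then about 273 with no drop-out and 259 if 5% contribute nothing. I use 266 as the lower figure and 295 as the upper.

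**3. Power within a stratum with E_s events:** Φ(|ln HR| × √E_s/2 − 1.96).
- 50:50, 266 events: E_s = 133, power 49%.
- 50:50, 295 events: E_s ≈ 148, power 54%.
- 70:30, 295 events: power 68% and 36%.
- 80% power in one stratum needs 276 events, nearly the whole trial's total.

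**4. Chance that exactly one of two strata is significant under one common effect:** p1(1 − p2) + p2(1 − p1).

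| Common HR | Events | Split | Exactly one significant |
|---|---|---|---|
| 0.714 | 266 | 50:50 | 50% |
| 0.714 | 295 | 50:50 | 50% |
| 0.714 | 266–295 | 70:30 | 55% |
| 0.714 | 295 | 90:10 | 70% |
| 0.714 | 375 (3 years for all) | 50:50 | 46% |
| 0.85 | 266 | 50:50 | 26% (p = 0.153 each) |
| 1.00 | any | any | 2 × 0.05 × 0.95 = 9.5% |

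A simulation of 1,000,000 draws (HR 0.714, 295 events) agrees: 49.7% at 50:50 and 55.2% at 70:30.

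**5. Interaction test.** In the same simulation it rejects 4.96% (50:50) and 5.01% (70:30) of the time under the common effect. The ratio of hazard ratios detectable with 80% power at 50:50 is exp(2.80 × √(4/148 + 4/148)) ≈ 1.9 with 295 events.

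**6. Haemoglobin within a half-sample stratum.** Patients per arm = 547/4 ≈ 137, difference 5 g/L, SD 11.3 g/L. Power = Φ(5/(11.3 × √(2/137)) − 1.96) ≈ 95%.

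**The case against.** The strongest reply is that the protocol contains no rule for concluding that effects differ, and nowhere says that p values will be compared across strata. Hazard ratios with intervals by stratum fit perfectly well with a forest plot and an interaction test. The ferritin and comorbidity entries are single lines in a condensed article, and a statistical analysis plan that is not shown may complete them. The interaction named for attendance shows that the authors know the tool.

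Much of this stands. A reader might infer that the trial will judge effect differences by separate within-stratum tests. The documents do not support that as a statement of fact, so the point is limited to the tool the protocol does name and what that tool tests. It is still more than a detail left to another document: the protocol specifies stratified comparisons, describes models with arm as the only covariate, assigns an interaction to one factor in addition to stratification, and makes a power claim about the strata. The arm-only sentence does not settle the matter alone, because the same section allows exceptions.

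The power sentence names no test and directly follows the haemoglobin calculation, so it may have been meant for haemoglobin only, where it is correct. It cannot be taken as proof of a subgroup method, but it does not limit itself to haemoglobin either.

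A reader might also take the figure of one half as general. It is not: it belongs to a common effect near the design value. Nor can a figure be given for at least one false contrast across all the subgroups. The protocol gives no prevalences or correlations, and does not make clear how many comorbidity categories there are.

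**Conclusion.** The point holds in limited form. As written, the protocol contains no test of whether the treatment effect differs by baseline ferritin, comorbidity or hepatitis B. The comparison it does state answers a different question.

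At the design hazard ratio, reading the strata by their p values would show a contrast where none exists about half the time, and more often with unequal strata. The size depends on the assumed split, on 266–295 events and above all on the true common effect: a weaker effect makes such contrasts less frequent, though still above the interaction test's 5%. The sentence on power within ferritin strata is not supported for the primary outcome.

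These are secondary analyses and the primary comparison is unaffected. The change is worth making because ferritin is the clinically central subgroup and the correction is nearly free.

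**What to change.** For baseline ferritin and each baseline comorbidity, fit one Cox model with arm, subgroup and their interaction. Base any claim of differential effect on the interaction estimate (ratio of hazard ratios) with its 95% confidence interval and p value. Present stratum-specific hazard ratios with confidence intervals descriptively, without within-stratum significance claims. The same test can be added for hepatitis B, noting that its status may be established at any time during the study and so is not purely a baseline variable.

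In the Sample size section, limit the statement on ferritin strata to haemoglobin, and give the primary-outcome power within a stratum with the split assumed.

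The cost is a few sentences, with no new data or patients. The real price is that subgroup claims become harder to make: the interaction test reaches 80% power only for a ratio of hazard ratios of about 1.9 at a 50:50 split. A non-significant interaction therefore must not be reported as evidence that the effects are equal.

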### Interim analyses {21b}

The DSMB will conduct an interim analysis after 288 patients have been randomised (i.e. at 50% recruitment) and followed for 24 months (2 years) following the date of the first patient randomised.

The interim analysis will review outcome data and answer the following questions:
Are there any significant safety issues that may present an ethical issue in continuing the study? This may include adverse events, but also study conduct and protocol violations.Is there overwhelming data suggesting the superiority of one arm that may present an ethical issue in continuing the study?Using the Haybittle-Peto rule, and the differences according to treatment allocation in risk of hospitalisation with all-cause infection or death as the outcome of interest, the study will be stopped early if there are differences according to treatment allocation in risk of hospitalisation with all-cause infection or death rate with a *p* value of less than or equal to 0.001.3.Are there any other factors that may impact on the feasibility / usefulness of the study? For example, rate of enrolment, unexpected low rate of outcomes, unable to fund and protocol violations.

### Methods for any additional analysis (e.g. subgroup analyses) {20b}

#### Factors associated with high ferritin

Associations at baseline will be explored using both ferritin as a continuous outcome and as a categorical dichotomous outcome (high and not high) using multivariable linear and log-binomial regression models respectively. Factors considered for associations with the outcome are serum hepcidin, TSAT, soluble transferrin receptor, percentage hypochromic red cells, reticulocyte haemoglobin content, liver iron, CRP, tumour necrosis factor alpha, IL1, IL6, infection rates, CV events, hepatitis, medications, comorbidities, dialysis vintage, dialysis access, hospitalisations and time variation of ferritin. Only variables significant at a nominal level *α* = 0.1 in univariable models will be included in a multivariable model. Variables will then be excluded from the multivariable models according to a stepwise backward selection method and a final multivariable model identified that include only variables with a *p* < 0.1. Variables in the multivariable models will be considered to have an independent significant statistical association with the outcome if their *p* value is < 0.01, variables with a *p* value between 0.1 and 0.01 will be considered border-line significant/show a weak signal of association with the outcome.

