#### Other outcomes assessed with non-randomized analyses

Assessment of *factors associated with high serum ferritin levels*: Association between ferritin and (a) other measures of iron status (serum hepcidin, transferrin saturation (TSAT), soluble transferrin receptor, percentage hypochromic red cells, reticulocyte haemoglobin content, liver iron), (b) Inflammatory markers (C-reactive protein (CRP), tumour necrosis factor alpha, interleukin 1 (IL1) and interleukin 6 (IL6)) and others (infection rates, CV events, hepatitis, medications, comorbidities, dialysis vintage, dialysis access, hospitalisations, time variation of ferritin)*Assessment of liver disease:* liver function tests *(*LFTs), hepatitis B status, ultrasound and FibroScan of the liver*Assessment of the comparability of the current ferritin assay platforms*: the Abbott ARCHITECT versus the Vitros® Ortho Clinical Diagnostics (OCD) platforms*Analysis of defined primary and secondary outcomes*: by average weekly dialysis attendance (according to both ordinal attendance group and using attendance as a continuous variable)*Analysis of defined primary and secondary outcomes*: by markers of inflammation

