## Data collection and management

### Plans for assessment and collection of outcomes {18a}

#### Demographic and clinical data

A full and relevant clinical and social history will be obtained from each participant. Key factors of direct interest for this study include time on dialysis, dialysis access and dialysis access interventions, ideal dry weight, height, body mass index, waist hip ratio, primary renal diagnosis, comorbidities (liver, lung, diabetes, cardiovascular, etc.), current smoking status, history of current or previous alcohol intake, dietary history, any significant illnesses, previous Hb levels, a full medication list and history, and sociodemographic data.

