#### Major events

Hospitalisation due to all-cause infections or death are documented as the primary outcome. All admissions overnight or longer are followed up with collection of detailed data on the admission. Data on all major vascular events, all dialysis access-related events including infections and vascular interventions not requiring hospital admission are also collected.

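### The model of baseline ferritin offers the variation of ferritin over time as an explanatory factor, which on most plain measures is tied to the outcome by construction; its event-type factors have no time window

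*Protocol article*

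**What the plan says.** Under 'Methods for any additional analysis {20b}', 'Factors associated with high ferritin', the protocol article sets the outcome: "Associations at baseline will be explored using both ferritin as a continuous outcome and as a categorical dichotomous outcome". The candidate factors are laboratory markers of iron status and inflammation and liver iron, followed by "infection rates, CV events, hepatitis, medications, comorbidities, dialysis vintage, dialysis access, hospitalisations and time variation of ferritin". The same section fixes the selection rules. A factor enters the multivariable model if its univariable test is significant at 0.1. Backward selection keeps factors with p < 0.1, and those with p < 0.01 are called independently associated with ferritin.

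The section 'Other outcomes assessed with non-randomized analyses' repeats the factors, including "hospitalisations, time variation of ferritin". Neither section gives a time window for the infection, event or admission factors, and neither says how variation of ferritin is measured.

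**The concern.** Two features do not fit a model declared to be at baseline.

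First, variation of ferritin over time is a function of repeated measurements of the outcome variable. If the chosen measure rises or falls with the level of ferritin, the model will declare it an independent factor whatever the biology. It will also absorb part of the effect of real markers, because a participant's SD carries information on that participant's ferritin level.

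Second, rates, event counts and admissions need a period of time. If that period were follow-up, the factors would come after the outcome that they are meant to explain, and randomised iron could affect them; treatment arm is not among the listed factors.

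At stake is the secondary objective on how ferritin relates to iron status, inflammation and liver disease, together with the stated aim of exploring the causes of hyperferritinaemia. No randomised comparison is involved.

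**Working it through.** The protocol gives no figure for this model, so there is none to reproduce.

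**Why the measure decides the result.** Suppose that a participant's ferritin is log-normal around a stable level, with within-person log-SD s. Then

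SD = mean × √(exp(s²) − 1), and CV = SD / mean = √(exp(s²) − 1).

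With s = 0.25 (an assumption), √(exp(0.0625) − 1) = 0.254. A participant with mean 800 μg/L has an SD of 0.254 × 800 = 203. One with mean 1600 μg/L has 0.254 × 1600 = 406. Both have a CV of 0.254. The SD follows the level and the CV does not. This holds whether the values come before or after baseline.

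For a change from baseline, Cov(F12 − B, B) = Cov(F12, B) − Var(B), where B is the baseline value and F12 the value at 12 months. With similar variances and a correlation below 1, this is negative. A slope that includes the baseline value behaves in the same way.

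**Size, with no real cause.**
- From the protocol: 576 participants, baseline ferritin 700 to 2000 μg/L, threshold p < 0.01.
- Assumed: log-normal ferritin, median 1100 μg/L, a stable level for each person, no treatment effect, 12 further monthly values, and four within-/between-person log-SD pairs (0.15/0.4, 0.25/0.4, 0.40/0.4, 0.25/0.2). Each was run 400 times.

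| Measure of variation | Mean correlation with baseline ferritin | Runs with p < 0.01 |
|---|---|---|
| SD of follow-up values, baseline excluded | 0.31 to 0.65 | 100% |
| SD of pre-baseline values, baseline excluded | 0.31 to 0.65 | 100% |
| Change from baseline to 12 months | −0.15 to −0.46 | 83 to 100% |
| Slope including baseline | −0.09 to −0.28 | 36 to 100% |
| CV, either window, baseline excluded | about 0.00 | 0 to 2% |

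For scale, p < 0.01 at n = 576 needs |r| > t/√(574 + t²). With t = 2.584 this is 2.584/√580.7 = 0.107. The smallest SD correlation, 0.31, is almost three times that.

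**Cost to a genuine marker.** One marker with a real effect of 0.10 log units per marker SD was added. Six scenarios were run 300 times each, with baseline ferritin regressed on the marker alone and then on the marker plus the SD of 12 later values.

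| Within / between log-SD, median | Marker coefficient lost to the SD | Marker at p < 0.01, without → with the SD |
|---|---|---|
| 0.15 / 0.4, 1100 | 57% | 87% → 31% |
| 0.25 / 0.4, 1100 | 54% | 69% → 19% |
| 0.40 / 0.4, 1100 | 46% | 34% → 10% |
| 0.25 / 0.2, 1100 | 29% | 100% → 96% |
| 0.25 / 0.3, 1150 | 44% | 96% → 51% |
| 0.15 / 0.2, 1150 | 34% | 100% → 100% |

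The SD itself was significant at 0.01 in every run. With the CV in its place, the marker's coefficient did not change.

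**The event factors.** Here there is no arithmetic, only the sections side by side.
- Towards follow-up: 'Major events' says "All admissions overnight or longer are followed up with collection of detailed data on the admission"; in Table 1 the row for clinical outcomes data starts at 3 months; and the factor list names cardiovascular events separately from comorbidities.
- Towards history: 'Demographic and clinical data' says "A full and relevant clinical and social history will be obtained from each participant"; Table 1 ticks hospitalisations at Day 1; and the monthly routine bloods include ferritin, so an earlier series can be retrieved.

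The text does not settle which is meant.

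**The case against.** The strongest reply is that the window and the variability measure are details for an analysis plan that is not shown, in an exploratory analysis that speaks of association and not of cause. For the window alone, much of that stands. It does not dispose of ferritin variation, because the protocol itself fixes the outcome, the factor list and the p-value rules, and a function of the outcome variable is on that list. Under the SD the problem is the same for either window.

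A second reply is that the coupling depends on a definition that the protocol does not give, and that the simulation inputs are assumed. Both are true. A CV that excludes the baseline value is clean, so the coupling is not inevitable, and the sizes are ranges under assumptions.

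A reader might go further and infer that the model explains baseline ferritin by events from follow-up, so that time is reversed. The protocol does not say this. It collects such events during follow-up, but that does not show that this model uses them, and the clinical history, the Day 1 entry for hospitalisations and the routine monthly bloods make a pre-baseline reading possible. Nor does the text support deleting the event factors: infection and admission history can be relevant correlates of an acute-phase protein.

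**Conclusion.** The point holds in a limited form. Variation of ferritin does not belong among the explanatory factors for baseline ferritin. As an SD, a change or a slope it is associated with the outcome without any real cause, and the SD also takes roughly 30 to 60% of a genuine marker's coefficient. These sizes rest on log-normal ferritin, a stable level for each person and the assumed spreads. The direction of the SD result needs only that the spread grows with the level.

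For infection rates, cardiovascular events and hospitalisations, the conclusion is conditional. The window is not fixed, and only a follow-up window would place them after the outcome and expose them to the effect of treatment.

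The correction is minor. The analysis is exploratory and non-randomised, and the primary result is unaffected.

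**What to change.** 1. Remove time variation of ferritin from the baseline ferritin model, and from the matching list under 'Other outcomes assessed with non-randomized analyses'. If it is of interest, describe it separately by arm as a coefficient of variation or as the SD of log-ferritin.
2. Keep infection, cardiovascular event and hospitalisation factors only as history from a stated window before randomisation.
3. Analyse such events after randomisation as outcomes, with baseline log-ferritin as exposure, adjusted for arm and the randomisation strata (location and ferritin stratum).

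The first and third changes cost wording only and use the same data. The second may need prior events to be extracted from existing hospital records, if they are not already captured at Day 1.

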#### Secondary objectives

The secondary objectives are as follows: (1) to document serious adverse events – major cardiovascular events, rates of infections and all-cause hospitalisation rates associated with the intravenous iron therapy [2]. To assess the relationship between ferritin, total body iron levels, measures of iron status, inflammation and liver disease [3]. To determine the costs that associate with intravenous iron treatment in this setting.

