### Participant timeline {13}

The participant timelines and scheduled visits are shown in Fig. 2 and Tables 1 and 2.

**Table 1 Tab1:** Schedule of visits, data collection and follow-up

Visit day	Pre-screen	Day 1 baseline	3 M	6 M	9 M	12 M	15 M	18 M	21 M	24 M	27 M	30 M	33 M	36 M
Visit Window			± 2 weeks	± 2 weeks	± 2 weeks	± 2 weeks	± 2 weeks	± 2 weeks	± 2 weeks	± 2 weeks	± 2 weeks	± 2 weeks	± 2 weeks	± 2 weeks
Check eligibility	x	x												
Informed consent		x												
Demographic data		x												
Medical history		x												
Dialysis history		x												
Sociodemographic history		x												
Randomise		x												
Blood test results^1^	x	x	x	x	x	x	x	x	x	x	x	x	x	x
Additional iron studies pathology^2, 3^		x	x							x				
MRI scan (FerriScan)^3^				x						x				
Ultrasound/FibroScan of the liver ^4^				x						x				
Clinical outcomes data collection			x	x	x	x	x	x	x	x	x	x	x	x
Vital status (alive)		x	x	x	x	x	x	x	x	x	x	x	x	x
Procedures		x	x	x	x	x	x	x	x	x	x	x	x	x
Hospitalisations		x	x	x	x	x	x	x	x	x	x	x	x	x
Concomitant medication		x	x	x	x	x	x	x	x	x	x	x	x	x
Adverse events		x	x	x	x	x	x	x	x	x	x	x	x	x

^1^ Monthly routine blood test results will be reviewed at all scheduled study time points

^2^FBC, Retics, CYTOK, ADIPO, STFR and HPCD

^3^MRI (FerriScan) will occur within 6 months of randomisation and again between 12 and 18 months from day 1 on approx. 100 willing participants

^4^Ultrasound (FibroScan) will occur within 6 months of randomisation and again between 12 and 18 months from day 1

^5^A comparison of ferritin assays will be performed at 1 month post randomisation on a small number of participants

**Table 2 Tab2:** Study timelines

	2019				2020				2021				2022				2023			
Quarter	1	2	3	4	1	2	3	4	1	2	3	4	1	2	3	4	1	2	3	4
Finalisation of protocol																				
Development of eCRFs																				
Ethics applications																				
Protocol Amendment 1																				
Site preparation																				
Recruitment																				
Participants follow-up																				
Data cleaning and analysis																				
Writing of paper(s)																				

This project will run until the end of 2023, with a predicted recruitment period of 2.5 years (see Table 2).

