### Methods in analysis to handle protocol non-adherence and any statistical methods to handle missing data {20c}

Both primary and secondary endpoints will be analysed according to the intention-to-treat principles (All participants data will be analysed according to the treatment allocation, regardless of what treatment they received and either they completed the follow-up or not). A secondary per-protocol analysis of all endpoints will be conducted. The per-protocol population will be all those who completed the treatment as allocated in the 2 groups.

Missing data will not be imputed. However, those with missing data will be described. This number is expected to be small (< 5% of randomised patients) and the same in each arm as maintenance haemodialysis patients attend haemodialysis three times per week, almost no First Nations dialysis patients leave the Northern Territory, and we will follow patients who move back to their community.

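### The factors-associated-with-ferritin rule gives every retained variable an association label using the p values that selected it; one candidate, liver iron, could cut the model to about 100 participants

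*Protocol article*

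**What the plan says.** The protocol's section on factors associated with high ferritin (under additional analyses, {20b}) models baseline ferritin twice: as a continuous outcome by linear regression, and as high or not high by log-binomial regression. The candidate list opens "Factors considered for associations with the outcome are serum hepcidin, TSAT, soluble transferrin receptor, percentage hypochromic red cells, reticulocyte haemoglobin content, liver iron, CRP" and runs to 19 items. Two of these, medications and comorbidities, are groups, so 19 is a minimum.

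The rule has three steps:

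- Screening: "Only variables significant at a nominal level *α* = 0.1 in univariable models will be included in a multivariable model".
- Elimination: "Variables will then be excluded from the multivariable models according to a stepwise backward selection method", giving "a final multivariable model identified that include only variables with a *p* < 0.1".
- Labelling: p < 0.01 in the multivariable model counts as an independent significant association. Variables between 0.01 and 0.1 "will be considered border-line significant/show a weak signal of association with the outcome".

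The section mentions no multiplicity control, shrinkage, validation or correction for selection. It does describe the associations as being explored.

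The analysis serves a stated secondary objective: "To assess the relationship between ferritin, total body iron levels, measures of iron status, inflammation and liver disease". On liver iron, footnote 3 of Table 1 has FerriScan done "on approx. 100 willing participants". Section {20c} says "Missing data will not be imputed" and expects missing data in fewer than 5% of randomised patients.

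**The concern.** The cut-off for staying in the model and the top of the weak-signal band are the same 0.1. Being retained therefore guarantees an association label, and the p value that awards the label is the one that selected the variable. P values and intervals reported after such a search are too favourable, and with this many candidates some retained variables are likely to be noise.

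Liver iron raises a second problem. It stands in the same list as routine blood tests but will be known for only a small consenting subset. If it passes the screen and the model is fitted to complete cases, the sample behind every other factor's estimate depends on that one screening result.

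At stake is how far readers can trust a published list of correlates of high ferritin in this population. The randomised comparison is not affected.

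**Working it through.** **Inputs**

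- Candidates: 19 listed items (factors section).
- Screening and retention thresholds: 0.1 each. Stronger label: p < 0.01 (same section). Two-sided tests are assumed.
- Participants: 576 in total (Abstract and Sample size). FerriScan: about 100 (Table 1, footnote 3).
- Correlation between candidates: not given. Assumed range 0 to 0.5.

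The plan states no error rate for this rule, so there is no figure to reproduce.

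**1. Independent candidates, none associated**

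- At least one label: 1 − 0.9^19 = 86.5%.
- At least one at p < 0.01: 1 − 0.99^19 = 17.4%.
- Expected number passing the screen: 19 × 0.1 = 1.9.
- If the grouped items expand the list to 22 or 30 variables: 1 − 0.9^22 = 90.2% and 1 − 0.9^30 = 95.8%.

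**2. The whole rule simulated under the same null**

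Univariable screen at 0.1, backward elimination to p < 0.1, then labels. Continuous ferritin, n = 576, 19 normal candidates with equal pairwise correlation, 4,000 replicates each:

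| Correlation | At least one label | At least one at p < 0.01 | Mean number labelled |
|---|---|---|---|
| 0 | 87.4% | 18.4% | 1.78 |
| 0.1 | 85.5% | 18.0% | 1.49 |
| 0.2 | 82.5% | 17.9% | 1.20 |
| 0.3 | 77.0% | 16.6% | 0.97 |
| 0.5 | 64.6% | 11.9% | 0.67 |

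Structures with correlated blocks of iron, inflammatory and clinical variables gave 76 to 83% for any label. Results at n = 100 were nearly the same (86.6% down to 65.1%), so the problem does not come from sample size. A second simulation gave 88%, 77% and 66% at correlations 0, 0.3 and 0.5, with the p < 0.01 label in 10 to 18% of runs.

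**3. Two codings of ferritin**

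Counting a label from either coding gave 81 to 96%, and a p < 0.01 label from either gave 19 to 30%. The dichotomy here was a median split, fitted with a linear approximation to the log-binomial model.

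**4. Some factors truly associated**

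With 6 true factors and 13 noise factors, at least one noise factor was labelled in 57 to 76% of runs. The effect sizes are assumptions, since the plan gives none. The independent-candidates formula, 1 − 0.9^13 = 74.6%, agrees with the upper end.

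**5. Liver iron**

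If liver iron is in a complete-case model, (576 − 100) / 576 = 82.6% of participants drop out. That also cannot fit the expectation in {20c} of under 5% missing, if that expectation was meant to cover this covariate.

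**6. The alternative**

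A full linear model with Benjamini-Hochberg control at 5% named at least one factor in about 5% of null runs. Leaving out liver iron and time variation of ferritin, 19 − 2 = 17 listed items remain: 576 / 17 ≈ 34 participants per term, or 576 / 25 ≈ 23 if the groups expand the model to 25 terms.

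**The case against.** **Exploratory status.** The section speaks of exploring associations, and the outcomes section places this work under non-randomised analyses. Screening without multiplicity control is weak but common in such work. This stands, and it limits the weight of the point.

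**Hedged labels.** The plan reserves its firm label for p < 0.01, which is stricter than 0.05, and words the rest cautiously. This also stands. Most of the 65 to 88% is the weaker tier.

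**The null is a benchmark.** The protocol's background itself describes ferritin as an iron-storage and acute-phase protein that rises with CRP, so it is implausible that nothing on the list is associated. A reader might infer that the rule will almost surely name noise factors, or will do so 80 to 90% of the time. The documents do not support that. The upper figures need near-independent candidates and no true association, and the case with six true factors gives 57 to 76%.

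**Exclusion is itself a result.** A reader might also infer that the rule can never report an absence of evidence. Variables dropped at screening or elimination are that report, and nothing says they will go unreported. The narrower statement holds: no variable in the final model can escape an association label.

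**Liver iron.** The loss depends on liver iron passing the screen and on one complete-case model being fitted, which the section does not say. The no-imputation sentence follows text about endpoints, and handling of a subset covariate may be left to an analysis plan not shown here. So the loss of about 83% is a possible consequence of the text, not a stated one.

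**Limits on the remedy.** Putting every listed item into both models would not be sound. Time variation of ferritin is derived from the outcome. The timing of infection rates, cardiovascular events and hospitalisations relative to baseline is not stated. A log-binomial model with 19 to 25 terms may not converge.

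**Conclusion.** The point holds as a minor one. The protocol itself fixes a rule in which selection and labelling use the same p values, and every retained variable receives a positive label.

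For one ferritin outcome and 19 candidates with no true association, at least one is labelled in about 65 to 88% of runs. With six true factors, a noise factor is labelled in about 57 to 76%. In practice this means roughly one or two spurious entries, mostly in the weak-signal tier; the p < 0.01 label appears in about 10 to 18% of null runs. These figures rest on the assumed correlations of 0 to 0.5, normally distributed candidates and, for the second range, assumed effect sizes.

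The liver-iron problem is conditional: about 100 of 576 participants would remain if that variable entered a single complete-case model.

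Neither part bears on the primary outcome or on any comparison between arms.

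**What to change.** For continuous ferritin, replace screening and backward selection with one pre-specified linear model containing the listed baseline factors. Leave out liver iron and any factor derived from ferritin itself (time variation of ferritin). Include event counts only if they are defined over a period before baseline. Report every estimate with its 95% confidence interval, claim association only at a 5% false discovery rate (Benjamini-Hochberg), and delete the 0.01 to 0.1 label.

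Treat the log-binomial model for dichotomised ferritin as supportive, with a smaller pre-specified set of factors. This section gives no cut-off for high ferritin, so the number of participants in that category, and hence the number of terms the model can carry, is unknown.

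Analyse liver iron in a separate model in the MRI subset with a few pre-specified adjusters, and report how many participants contribute.

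The cost is a change of wording and one extra model. No new data are needed. Fewer factors will be named, and strongly correlated markers kept together in one model will have wider intervals.
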